### Statistical analysis

All statistical analyses will be performed using the R statistical software (ver. 4.3.0, R Development Core Team, 2023) and SAS (ver. 9.4, The SAS Institute, Cary, NC, USA).

Categorical variables will be described using frequency distributions and percentages. The number of missing data will be indicated, but will not be taken into account for the calculations. Quantitative data will be described using the number of observations, mean, standard deviation, median, minimum and maximum values. The date of randomization will be considered as the reference date in all time calculations unless otherwise specified. An ITT analysis will be used to avoid attrition bias. Data at inclusion will be described in the ITT population and presented by the randomization arm. Results will be considered significant when the *p*-value is less than or equal to 0.05, except for the primary endpoint (alpha set at 0.025).

For the primary endpoint, the minimal important difference (MID) will be set to 10 points for each fatigue score (physical and cognitive) (MID = 0.5*SD) [56, 57]. These dimensions of the EORTC QLQ-FA12 will be analysed at 3 years. A Student-t test will be used to compare the scores between the two arms at 3 years, adjusting for the level of HRQoL at inclusion. In case of non-normal distribution, a non-parametric Mann-Whitney test will be performed. An analysis of the missing data profile at baseline and during follow-up will be performed to determine the missing data profile. An effort will be made to have all patients complete the baseline questionnaire as well as the 3-year questionnaire, to ensure the statistical power for the primary analysis. Stratified analyses will be performed according to stratification criteria of the randomisation.

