### Study objectives

Objective 1: to investigate the impact of a one-year supervised PA program implemented concomitantly with first-line cisplatin-based chemotherapy, on CRF (primary outcome, both physical and cognitive aspects of CRF at 3 years) and other short- and long-term sequelae (secondary outcomes: another dimension of CRF– emotional fatigue, HRQoL, cognition, anxiety/depression, anthropometry, physical condition, PA/sedentary behaviour level, pain and neuropathy, sustainable return to work, sleep quality, heart rate, TGCT relapse, cardiovascular toxicities, secondary primary malignancy, immune/inflammatory/liver function biomarkers) in first-line metastatic TGCT patients (Hypothesis 1).

Objective 2: to investigate how the gut microbiota (diversity and taxonomic composition) and its metabolites involved in the gut-brain axis (e.g., SCFAs, bile acids, GABA, tryptophan metabolites including serotonin) mediate the impact of PA on primary and secondary outcomes in metastatic TGCT patients receiving chemotherapy (Hypothesis 2).

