## Statistical considerations

### Sample size

In order to evaluate our primary endpoint and to detect a minimum significant difference ≥ 10 points in the CRF scores between the 2 groups at 3 years, with a standard deviation of 20, considering 2 dimensions of CRF (physical and cognitive fatigue) assessed by the EORTC QLQ-FA12 questionnaire, with a bilateral alpha, type I error of 0.025 (Bonferroni adjusted *p*-value for two targeted dimensions, overall risk of 5%), a statistical power of 90%, 200 patients with fatigue scores available at baseline and 3 years is required. Considering 15% of lost to follow-up or unavailable data and patients without fatigue scores available, 118 patients per group will be randomized (1:1), for a total of 236 patients.

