### Decision rule

A single sufficient decision rule will be taken to interpret the results: the primary endpoint will be considered to be reached if at least one dimension among the two targeted ones (physical and cognitive fatigue) will be statistically significant in favour of the intervention arm, in absence of a statistically significant negative result on the other dimension.

For secondary endpoints, data at randomization will be compared between the 2 arms, and then the absolute and relative variations between inclusion and the different measurement times will be described and compared by arm. Longitudinal analysis of HRQoL will be performed by including all available measurement time until Y3. A mixed model for repeated measures will be performed including the randomized group, time, and intervention by time interaction, as well as random effect on intercept and time to reflect the individual deviance at baseline and over time. The proportion of patients with stable, deteriorated, and improved HRQoL using the MID at M12, and at Y3. Each HRQoL score from the EORTC questionnaire will be analysed. The MID will be fixed to 10 points for each HRQoL score of the EORTC questionnaires. Time to improvement or deterioration of HRQoL could also be proposed in complement using Kaplan-Meier survival estimation [58, 59]. A detailed statistical analysis plan will be written for each endpoint before the data is frozen.

For the gut microbiota study, to investigate whether the gut microbiota and its metabolites mediate the positive effect of PA on CRF and other short- and long-term sequelae in metastatic TGCT patients receiving chemotherapy, we will apply two steps of statistical analyses overall: Step 1 to test “the impact of PA on the chemotherapy-induced alterations in the gut microbiota and relevant metabolites” and Step 2 to test “the effect of the gut microbiota and relevant metabolites modulated by PA on CRF and other short- and long-term sequelae in metastatic TGCT patients receiving chemotherapy”.

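### The blanket p ≤ 0.05 rule lets any secondary result be called significant; across the 28 EORTC quality-of-life scores alone, a chance finding has roughly a one-in-three to two-in-three probability

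*Protocol article*

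**What the plan says.** All references are to the protocol article.

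- **Sample size.** The two primary fatigue dimensions (physical and cognitive, EORTC QLQ-FA12 at 3 years) are planned "with a bilateral alpha, type I error of 0.025 (Bonferroni adjusted" for two dimensions), giving an overall risk of 5%.
- **Statistical analysis.** One general rule governs the word *significant*: the p "value is less than or equal to 0.05, except for the primary endpoint (alpha set at 0.025"). Only the primary endpoint is exempted from 0.05.
- **Study objectives.** The secondary outcomes begin with "emotional fatigue, HRQoL, cognition, anxiety/depression, anthropometry, physical condition" and continue through activity level, pain, return to work, sleep, relapse, late toxicities and biomarkers.
- **Decision rule, secondary endpoints.** "the absolute and relative variations between inclusion and the different measurement times will be described and compared by arm". HRQoL is also analysed longitudinally to year 3 with a mixed model, and "Each HRQoL score from the EORTC questionnaire will be analysed".
- **Decision rule, primary endpoint.** Success depends only on physical and cognitive fatigue. No secondary outcome enters it.
- **Decision rule, other.** A detailed statistical analysis plan for each endpoint is promised before the data are frozen. The gut microbiota part corrects the taxonomic comparisons by Benjamini–Hochberg.

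The article does not label any secondary outcome as key or exploratory, and does not make any of them conditional on the primary result.

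**The concern.** The issue is a rule that the article states, not merely a detail it leaves out. By exempting only the primary endpoint, the sentence fixes how every other result will be described: at p ≤ 0.05 it is significant. With at least 28 quality-of-life scores to analyse, that wording invites a claim of benefit on whichever score happens to cross the line.

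What is at stake is the standing of the secondary conclusions. The first study hypothesis covers cognitive, psychological, clinical and metabolic sequelae and quality of life as well as fatigue. A reader of the results would have no means, from the stated rule, of telling a planned and error-controlled secondary finding from one picked out of many.

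**Working it through.** **1. Reproduce the plan's own figures (Sample size).** Inputs: a difference of "10 points in the CRF scores between the 2 groups at 3 years", "with a standard deviation of 20", two-sided alpha 0.025, power 90%.

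- n per arm = 2 × SD² × (z₀.₉₈₇₅ + z₀.₉₀)² / difference² = 2 × 400 × (2.241 + 1.282)² / 100 = 99.3, rounded up to 100, so 200 in total.
- Power at 100 per arm: 90.2% by the normal approximation, 89.8% by the exact noncentral t.
- Loss of 15%: 100 / 0.85 = 117.6, rounded up to 118 per arm, so 236 in total.
- Primary family: 0.025 + 0.025 = 0.05.

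The stated 200, 236 and 5% all reproduce.

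**2. Count the scores (Secondary study outcome).**

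- QLQ-C30: 5 functioning scales + 1 global scale + 3 symptom scales + 6 single items = 15.
- QLQ-TC26: 7 domains + 6 single items = 13.
- Total: 28.

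This leaves out FACT-Cog, HADS, fitness tests, anthropometry, pain scales, biomarkers and emotional fatigue.

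**3. Error rates, one two-sided test per score at 0.05, all null hypotheses true.**

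- Expected number of false significant scores: 28 × 0.05 = 1.4, whatever the correlation.
- At least one, independent tests: 1 − 0.95²⁸ = 76.2%.
- At least one favouring the programme, independent tests: 1 − 0.975²⁸ = 50.8%.

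The scores will be positively correlated, but the article gives no correlations. They were therefore assumed equal (ρ) and simulated, with 200,000 draws per case: Zⱼ = √ρ·C + √(1−ρ)·Eⱼ, where C and Eⱼ are independent standard normals. A score was counted when |Zⱼ| > 1.96, or when Zⱼ was beyond 1.96 in the favourable direction (scores oriented the same way).

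| Assumed correlation | Any false significant score | A false score favouring the programme |
|---|---|---|
| 0 (formula) | 76% | 51% |
| 0.3 | 64% | 34% |
| 0.5 | 49% | 25% |
| 0.7 | 33% | 17% |

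These figures use one visit and one method per score. The article foresees comparisons at several visits, on both absolute and relative change, as well as a mixed model. Further tests of the same scores can only raise the rates; that increase was not calculated.

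**4. For scale.** Bonferroni control of the 28 scores at 5% would need 0.05 / 28 = 0.0018 per score, against the 0.05 stated.

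**The case against.** The strongest reply is that ordering, gating and labelling of secondary endpoints are commonly left to the statistical analysis plan. The article promises one for each endpoint before data freeze and is itself a condensed account. This stands as far as it goes: the absence of a hierarchy is no finding. It does not answer the sentence that is present. The promise does not say that multiplicity is deferred, and an analysis plan faithful to the article would carry the flat 0.05 forward. The article also states corrections where it intends them, Bonferroni for the primary dimensions and Benjamini–Hochberg for taxa, and the latter does not reach the listed secondary endpoints.

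Three stronger readings are tempting, and the document does not support them.

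- *A reader might infer that the trial's 5% risk is breached.* It is not. The decision rule rests only on physical and cognitive fatigue, each at 0.025. If both fail, no secondary result makes the trial positive.
- *A reader might infer that emotional fatigue is wrongly given a looser alpha.* The 0.025 is half of a Bonferroni split over two named dimensions, and emotional fatigue is a secondary outcome outside that family. Adding it at 0.05 takes the three QLQ-FA12 dimensions to at most 0.025 + 0.025 + 0.05 = 0.10 (0.097 if independent), but the article promises no 5% guarantee for that wider set.
- *A reader might infer that a false claim of benefit is likely.* At a correlation of 0.5 the figure for a false result favouring the programme is 25%. It exceeds one half only if the tests are independent.

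Nor should the proportions of improved, stable and deteriorated patients be counted as additional tests: the article names no test for them.

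**Conclusion.** The point holds as a minor one. The stated rule allows every non-primary result to be declared significant at 0.05, and for the 28 EORTC quality-of-life scores alone the chance of at least one false declaration is about 49%, with 64% to 33% over assumed correlations of 0.3 to 0.7. For a false declaration in favour of the programme it is about 25% (34% to 17%).

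The count of 28 comes from the article. The correlations, their equality and the single test per score are assumptions. Even at the highest correlation examined, the overall rate is several times 5%. What is affected is the wording and weight of the secondary conclusions, not the primary analysis, its error rate or the number of patients.

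**What to change.** Restrict the sentence on significance in Statistical analysis, along these lines:

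> Each of the two primary fatigue dimensions is tested at a two-sided level of 0.025. Secondary endpoints are exploratory: they are reported as differences between arms with 95% confidence intervals and nominal p-values, and are not declared significant, unless the statistical analysis plan specifies, before data freeze, a list of secondary endpoints with control for multiplicity.

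Whether to have such a list, and how to order or gate it, is the sponsor's choice and is not needed to resolve this point. If a list is made conditional on the primary result, the two-way Bonferroni split passes on only 0.025 when one dimension succeeds and 0.05 when both do.

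The cost is a change of wording in the protocol and the analysis plan. It needs no extra patients or data and does not alter the sample size of 236. The small downside is that most secondary results could no longer be called significant.

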### Randomization

At the first visit of the study (D0), patients will be randomly assigned (1:1 ratio) to one of the following arms: (1) Intervention arm - patients will receive PA recommendations at baseline, and a one-year PA program based on supervised sessions, motivational interviews and a connected activity tracker to wear during the whole intervention or (2) Control arm - patients will receive PA recommendations at baseline and a connected activity tracker to wear during one year.

Randomization will be stratified on (1) tumour classification: good vs. intermediate vs. poor prognosis [3, 4]; (2) PA level at inclusion assessed by the French National Observatory for PA and Sedentariness PA Questionnaire (ONAPS-PAQ), which is developed and validated to assess PA and sedentary behaviours in the French general population [34]: inactive vs. active vs. very active; (3) patient age: less than 40 years vs. 40 years and older.

An online randomization platform (Ennov Clinical Software) will be used to confirm the eligibility of the patient, indicate the criteria for stratification and proceed with randomization. The result of the randomization will be available immediately and a confirmation email will be automatically sent to the research staff of the investigating centre and the coordinating centre.

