### Analysis population

Statistical analyses will be performed on the Intent-to-Treat (ITT) population, including all randomized patients analysed according to the randomization scheme. A sub-population will be defined for the analysis of the primary endpoint, corresponding to a modified ITT population, i.e., all ITT patients with at least the available fatigue score at baseline and 3 years.

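### The primary analysis is mis-stated: the named tests take no covariate, the HRQoL covariate is not one variable, and the required baseline fatigue score is not used

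*Protocol article*

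**What the plan says.** The Statistical analysis section of the protocol article sets the primary comparison in one sentence: a "Student-t test will be used to compare the scores between the two arms at 3 years, adjusting for the level of HRQoL at inclusion". The next sentence gives the fallback: "In case of non-normal distribution, a non-parametric Mann-Whitney test will be performed". The same paragraph ends with "Stratified analyses will be performed according to stratification criteria of the randomisation", without saying what these analyses are for.

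Three other sections bear on this:

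- **Analysis population** restricts the primary analysis to "all ITT patients with at least the available fatigue score at baseline and 3 years". **Sample size** counts patients in the same way: "a statistical power of 90%, 200 patients with fatigue scores available at baseline and 3 years is required".
- **Randomization** stratifies on three factors, beginning: "Randomization will be stratified on (1) tumour classification: good vs. intermediate vs. poor prognosis". The other two are physical activity (PA) level (three classes) and age (under 40 or not).
- **Primary study outcome** and **Secondary study outcome** treat fatigue (QLQ-FA12) and HRQoL (QLQ-C30 and QLQ-TC26) as separate outcomes with separate instruments.

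**The concern.** The sentence that defines the confirmatory test of a phase III trial can be read in at least two ways. It may mean a plain t-test with the adjustment dropped, or a linear model with some HRQoL score as covariate. The two give different estimates, standard errors and p-values. Under the second reading the covariate still has to be chosen from many scores. If the data look non-normal, the fallback drops any adjustment without saying so, and that switch depends on the observed data.

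The design also points to a covariate that the test does not use. Patients without a baseline fatigue score are removed from the primary population, yet that score plays no part in the stated comparison. Baseline values of the outcome and the stratification factors are the usual sources of precision in such a trial. Leaving them out gives wider intervals than necessary and leaves any chance imbalance in baseline fatigue uncorrected.

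**Working it through.** **1. Count the possible covariates (Secondary study outcome).** QLQ-C30: 5 functioning + 1 global + 3 symptom scales + 6 single items = 15. QLQ-TC26: 7 domains + 6 single items = 13. Total 15 + 13 = 28 scores. The primary analysis sentence names none of them.

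**2. Reproduce the planned sample size.** Inputs from the Sample size section: difference 10, SD 20, power 90%, 1:1 allocation, 15% loss, and the error rate set "with a bilateral alpha, type I error of 0.025 (Bonferroni adjusted" for two dimensions.

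n per arm = 2 × (z₀.₉₈₇₅ + z₀.₉₀)² × (20/10)² = 2 × (2.241 + 1.282)² × 4 = 99.3, so 100 per arm and 200 in total. Inflated for loss: 200/0.85 = 235.3, so 236.

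Both stated figures reproduce. They are those of an unadjusted comparison on the raw SD. With the noncentral t distribution, power at 100 per arm is 89.8% (normal approximation 90.2%).

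**3. Effect of using the baseline score.** With correlation r between the baseline and 3-year score of the same dimension, the residual SD is 20 × √(1 − r²) and the standardised difference is 0.5/√(1 − r²). The equivalent unadjusted sample is 100/(1 − r²) per arm. The protocol gives no r, so a range is assumed. Noncentral-t power, 100 per arm, two-sided alpha 0.025:

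| Assumed r | Residual SD | Power | Equivalent n per arm |
|---|---|---|---|
| 0 (unadjusted) | 20.0 | 89.8% | 100 |
| 0.2 | 19.6 | 91.0% | 104 |
| 0.3 | 19.1 | 92.5% | 110 |
| 0.4 | 18.3 | 94.4% | 119 |
| 0.5 | 17.3 | 96.5% | 133 |

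The gain is about 1 to 7 percentage points. The few degrees of freedom spent on covariates are ignored; with 200 patients this is negligible.

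**4. Effect of leaving the stratification factors out of the test.** Suppose they explain a share R² of the outcome variance (assumed; the protocol gives none). Stratified randomisation then makes the true variance of the difference smaller than the unadjusted test estimates. By the normal approximation:

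- actual alpha = 2 × [1 − Φ(2.241/√(1 − R²))]
- unadjusted power = Φ((3.536 − 2.241)/√(1 − R²)), where 3.536 = 10/(20 × √(2/100))
- adjusted power = Φ(3.536/√(1 − R²) − 2.241)

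| Assumed R² | Actual alpha, unadjusted | Power, unadjusted | Power, adjusted |
|---|---|---|---|
| 5% | 0.0215 | 90.8% | 91.7% |
| 10% | 0.018 | 91.4% | 93.1% |
| 20% | 0.012 | 92.6% | 95.7% |

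The unadjusted test is conservative and does not exceed its nominal level.

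**The case against.** The strongest reply is that this is loose wording for a workable analysis: a linear model in which the arm coefficient is tested with a t statistic. That is a plausible intent, and it is why the sentence should not be read as proof that no analysis is possible. It does not settle which covariate is meant, and the Mann-Whitney fallback still could not carry the adjustment.

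A reader might go further than the document allows in four ways.

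- **That the trial is underpowered.** It is not. The stated 90% rests on an unadjusted test and reproduces.
- **That HRQoL is a wrong or biasing covariate.** Adjusting for any baseline variable leaves a randomised comparison unbiased. QLQ-C30 contains fatigue and cognitive scales, so such a covariate might recover part of the precision. The Decision rule section also speaks of HRQoL scores of the EORTC questionnaires. FA12 is an EORTC questionnaire, so the intended covariate may even be the baseline fatigue score. The term is ambiguous; it is not shown to be wrong.
- **That the stratification factors are ignored.** Stratified analyses are planned. What is missing is their role: adjusted primary analysis, sensitivity analysis or subgroups.
- **That the analyst will choose freely once results are known.** The Decision rule section promises a detailed analysis plan before the data are frozen. In an open-label trial this does not guarantee that the choice precedes all data, but it is a safeguard.

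One could also say that the choice of covariate belongs in that later plan. That would hold if the protocol were silent. Here it names a test, an adjustment and a fallback that do not fit together.

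**Conclusion.** The point holds as a defect in how the primary analysis is stated. Neither named test can adjust for a covariate, the covariate is one of 28 unnamed scores if HRQoL is taken as the protocol describes it, and the baseline fatigue score that defines the primary population is not used. The stratification factors are outside the primary comparison as written.

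The consequence is an ambiguous confirmatory test and forgone precision. Planned power is intact at 89.8% unadjusted. The gain from ANCOVA, to between 91% and 96.5%, rests wholly on assumed correlations of 0.2 to 0.5 over three years from the start of chemotherapy. It is measured against an unadjusted test, so it overstates the gain over an HRQoL-adjusted model. The case for the change rests first on removing the ambiguity and second on precision that costs nothing.

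**What to change.** Replace the primary analysis sentence and its fallback with text along these lines:

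*For each of the two dimensions (physical and cognitive fatigue), the Y3 FA12 score will be analysed by linear regression (ANCOVA) with arm, the D0 score of the same dimension, prognosis group, PA level and age group as covariates. The adjusted mean difference with its 97.5% confidence interval is the primary result, tested at two-sided alpha 0.025. An unadjusted t-test and a rank-based or robust analysis are pre-specified sensitivity analyses.*

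This replaces the HRQoL covariate and removes the normality-dependent switch to Mann-Whitney as the primary test. State separately what the planned stratified analyses are for.

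The cost is wording only. All covariates are already collected at inclusion, no visit or patient is added, and 200 evaluable and 236 randomised patients remain sufficient.

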#### Secondary study outcome

*Other dimensions of CRF* [Time points: D0, end CT (M3), M6, M12, then annually until Y10]: CRF will be assessed by the EORTC QLQ-FA12 [37]. Participants will be asked to rate their fatigue to a 4-point Likert scale ranging from “not at all” to “very much”. All the scores will be converted to a scale from 0 to 100, with higher scores indicating greater degrees of CRF.

*Health-related Quality of Life (HRQoL)* [Time points: D0, end CT (M3), M6, M12, and then annually until Y10]: HRQoL will be assessed by the EORTC QLQ (QLQ-C30), with 30 items categorized into five functioning scales (physical, role, cognitive, emotional, and social), a global QOL scale, three symptom scales (fatigue, nausea/vomiting, and pain) and six single symptom items (dyspnoea, insomnia, appetite loss, diarrhoea, constipation, and financial difficulties) [38, 39]. In addition, the testicular cancer-specific HRQoL will be assessed by EORTC QLQ-TC26 [40], with 26 items organised into 7 domains and 6 single items addressing: treatment side effects, treatment satisfaction, future perspective, work/education problems, physical limitations, infertility, family problems, sexual activity, sexual enjoyment, sexual problems, communication, body image problems and testicular implant satisfaction. Participants will be asked to respond to a Likert scale ranging from “not at all” to “very much” or from “very bad” to “excellent”. Subsequently, all the scores will be standardized on a scale of 0 to 100, with higher scores representing better functioning, better HRQoL and greater symptom burden.

*Cognition* [Time points: D0, end CT (M3), M12, Y2, and Y3]: Cancer-related cognitive disorders will be assessed by the Functional Assessment of Cancer Therapy-Cognitive Function (FACT-Cog) questionnaire [41]. The FACT-Cog is a validated self-administrated questionnaire to evaluate memory, attention, concentration, language, and thinking abilities. It consists of 37 items with four subscales: patients’ perceived cognitive impairments, perceived cognitive abilities, deficits observed or reported by others, and impact of cognitive changes on HRQoL. Participants will rate how often these situations occurred during the last seven days on a Likert scale ranging from “never” to “several times a day”, with higher scores indicating better perceived cognitive function.

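### The primary test switches from a baseline-adjusted comparison of means to a plain Mann-Whitney test if scores look non-normal, dropping the adjustment and the 10-point target; one fixed ANCOVA avoids this at no cost

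*Protocol article*

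**What the plan says.** The Statistical analysis section of the protocol article sets the primary comparison in two sentences. The first names a Student t test of the year-3 scores by arm, adjusted for baseline HRQoL. The second makes it conditional: "In case of non-normal distribution, a non-parametric Mann-Whitney test will be performed". For the rank branch the article names no covariate and no effect measure.

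The design target is a difference in means. The Sample size section plans "to detect a minimum significant difference ≥ 10 points in the CRF scores between the 2 groups at 3 years". It assumes an SD of 20 and, for each of the two dimensions, works "with a bilateral alpha, type I error of 0.025". The Statistical analysis section repeats the target: "the minimal important difference (MID) will be set to 10 points for each fatigue score".

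On the scores, the Secondary study outcome section describes 4-point items and adds "All the scores will be converted to a scale from 0 to 100, with higher scores indicating greater degrees of CRF". The Primary study outcome section gives 12 items for the whole instrument; items per dimension are not stated. The Decision rule section counts the trial as positive if at least one of physical and cognitive fatigue is significant in favour of the intervention and the other is not significantly worse.

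**The concern.** The rule lets the observed outcome distribution decide which analysis is confirmatory, and the two branches answer different questions. The first compares means after adjustment for a baseline covariate. The second is a plain Mann-Whitney test. It takes no covariate and tests whether a patient in one arm tends to score higher than a patient in the other. It reads as a shift in points only if the two distributions have the same shape, which bounded scores with a floor need not have.

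Three things are at stake if the rank branch is used:

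- The stated baseline adjustment disappears.
- The p-value no longer refers to the 10-point mean difference used for the sample size and the MID.
- The check could go one way for physical fatigue and the other way for cognitive fatigue, so one decision rule would combine two tests with different targets.

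The scores are averages of a few four-category items, so a formal normality check may well send the trial down this branch.

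**Working it through.** **1. The plan's own figure.** Inputs from the Sample size section: difference 10, SD 20, two-sided alpha 0.025, power 90%, 1:1 allocation, 15% loss.

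- n per arm = 2 × (z₀.₉₈₇₅ + z₀.₉₀)² × SD² / difference² = 2 × (2.2414 + 1.2816)² × 400 / 100 = 99.3, so 100 per arm and 200 in total.
- 200 / 0.85 = 235.3, so 236, or 118 per arm.

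Both stated figures reproduce. The formula has no covariate, so the plan is sized as an unadjusted comparison of means. Power at 100 per arm is Φ(10 / (20 × √(2/100)) − 2.2414) = Φ(3.5355 − 2.2414) = 90.2%.

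**2. How often would the switch fire?** With k four-category items, a dimension score takes 3k + 1 values in steps of 100/(3k) points: 7 values 16.7 points apart for k = 2, and 19 values 5.6 points apart for k = 6. Assumptions, none of them from the article: k = 2 to 6, latent inter-item correlation 0.6, three sets of category thresholds, and Shapiro-Wilk at 0.05. There were 100 patients per arm and 1,000 simulated trials per setting.

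| Distribution | Items | Rejected in either arm | Rejected on pooled residuals |
|---|---|---|---|
| Symmetric (mean about 50) | 2-3 | 100% | 100% |
| Symmetric | 4 | 98% | 99% |
| Symmetric | 5 | 88% | 96% |
| Symmetric | 6 | 76% | 90% |
| Mild right skew (10-24% at zero) | 2-6 | 100% | 100% |
| Floor (28-48% at zero) | 2-6 | 100% | 100% |

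The Background cites a fatigue prevalence of 15% after diagnosis and 27% at a median of 19 years. That makes low scores and right skew plausible but does not establish them.

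**3. Does non-normality require the switch?** In the same kind of simulation (2 and 5 items, latent baseline-to-year-3 correlation 0.4 or 0.7), the type I error of the t test, Mann-Whitney and ANCOVA lay between 0.019 and 0.031 against a nominal 0.025, floor-heavy scores included. At this size the comparison of means holds its level.

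**4. What the switch costs in power.**

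- Rank test against unadjusted t test: on normal data the relative efficiency is 0.955, so power is Φ(3.5355 × √0.955 − 2.2414) = Φ(1.2136) = 88.8%, against 90.2%. In the simulations the two were within about 3 points.
- ANCOVA: residual SD = 20 × √(1 − r²), where r is the correlation of the baseline covariate with the year-3 score. The article gives no r.

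| Assumed r | Variance removed (r²) | ANCOVA power, n = 200 |
|---|---|---|
| 0 | 0% | 90.2% |
| 0.3 | 9% | 92.9% |
| 0.5 | 25% | 96.7% |
| 0.7 | 49% | 99.7% |

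In the simulations Mann-Whitney trailed ANCOVA by 0 to 6 points at latent r = 0.4 and by 5 to 22 points at r = 0.7. For example, with 5 items, mild skew, r = 0.7 and a true difference of about 7.9 points, power was 58.7% against 78.1%.

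**The case against.** The strongest reply has four parts.

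- **The detail belongs in the analysis plan.** The Decision rule section promises one for each endpoint before the data are frozen. The normality criterion, an effect measure for the rank branch and a common test for both dimensions could all be settled there. This stands: their absence from a journal article is no fault. But the switch itself is stated here as the rule for the primary analysis, and a later plan that follows the protocol would keep it. The stratified analyses by randomisation factor do not bring back the HRQoL adjustment.
- **The switch is not certain to fire.** A reader might infer from the simulations that it is. The documents do not support that. They name no normality test and give no score distribution; a visual check would be less predictable, and symmetric scores with 5 or 6 items sometimes pass.
- **Little is lost.** The sample size never relied on adjustment, and the rank test is about one point below planned power. This also stands. The r² reduction is a forgone gain, not a loss of planned power. Its size is unknown, since the covariate is pre-chemotherapy HRQoL and the outcome is fatigue three years later.
- **The result could still be read against the MID.** A reader might infer that no estimate would remain. But the article plans means and SDs for quantitative data, so arm means would be described, and the decision rule asks only for significance. What goes is the mean difference as the adjusted and tested quantity.

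**Conclusion.** The point holds in a limited form and is a free improvement, not a threat to validity. The protocol ties its confirmatory test to the observed distribution, and the alternative branch drops the stated covariate and leaves the quantity on which the trial was sized. Under a formal normality test the switch is likely (76-100% for symmetric scores, about 100% for skewed ones). This rests on assumed item counts, thresholds and inter-item correlation.

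The cost is the changed target, the possible mismatch between the two dimensions, and an efficiency gain given up: about 93-97% power with ANCOVA at an assumed r of 0.3-0.5, against about 89% for the unadjusted rank test.

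A reader might also infer an inflated false-positive rate or a test chosen with hindsight. Neither is shown. Each test held its level when applied on its own, although the two-stage procedure as a whole was not simulated. A check that rejects almost every time would in effect fix the test in advance.

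**What to change.** Delete the conditional sentence. In its place, name one linear model (ANCOVA) of the year-3 score on arm and a stated baseline covariate, used for both physical and cognitive fatigue whatever the distribution. This also settles the wording of the first branch, since a Student t test cannot itself adjust for a covariate. The protocol names HRQoL at inclusion; the baseline fatigue score is by definition available for every patient in the modified ITT population. The text should say which is used.

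Report the adjusted mean difference with a 97.5% confidence interval, matching the alpha of 0.025 per dimension, and heteroscedasticity-robust standard errors. Keep the Mann-Whitney test only as a pre-named sensitivity analysis.

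The cost is a sentence or two in the Statistical analysis section. No extra data are needed, and the 236 patients stand, because even with r = 0 the model gives 90.2% power at 200 evaluable patients.
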